### Randomization and Allocation Sequence Generation

The earlier estimated sample size of 86 is increased to 88 children with overweight to have an equal balance in each group of the treatment.

#### Randomization Procedure for 88 Participants (44 Each Group)

For a total sample size of 88 overweight patients (44 in each group: Navak Guggulu and Vachaharidradi Gana Vati), block randomization will be used to ensure balanced allocation throughout the study [45]. A block size of 4 will be used, dividing the sample size into 22 blocks. Each block will consist of predefined sequences, such as AABB, ABAB, BABA, or BBAA, where “A” represents group A (Navak Guggulu) and “B” represents group B (Vachaharidradi Gana Vati). These sequences ensure that within each block, participants are equally allocated to both groups. The randomization sequence will be generated using a computerized random number generator or statistical software, ensuring variability in block order. The randomization process will be managed by a trained, unblinded departmental faculty member who is not involved in the study. The block randomization procedure ensures that both groups maintain equal sample sizes while preventing predictability, preserving the study’s internal validity and robust design.

#### Allocation Implementation

To maintain allocation concealment, the group assignments will be placed in SNOSE, with each envelope containing 1 allocation based on the pregenerated sequence. The SNOSE technique is widely used in clinical trials [46]. The process of assigning treatments to these envelopes will be conducted by personnel not involved in enrolling or assessing participants. To maintain blinding, treatments will be labeled with coded identifiers. Treatments A and B will be recoded by unblinded, trained faculty using either code III or code IIII. This unblinded faculty will not be involved in the trial’s conduct and assessment. The blind code III or IIII will be labeled on the respective patient numbers on the opaque containers by the trained, unblinded faculty. These recoded opaque containers will then be handed over to the investigator for further administration to the patients. An unblinded, trained faculty will also provide 88 sealed envelopes to the investigator, containing unblinded information about the treatment administered to each patient. These sealed envelopes will be kept intact under the investigator’s custody until the completion of the last visit of the last enrolled patient in the study and stored in a manner that prevents accidental disclosure. A master chart will be prepared as a data source for statistical analysis and will be handled with high security, ensuring confidentiality and limited access to authorized personnel only. When the data have been locked, the outcome assessor (statistician) will unblind the treatment codes for statistical analysis.

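### Group codes III/IIII on patient-numbered containers, combined with fixed blocks of four, make the code sequence partly predictable, contrary to the protocol's own claim

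*Protocol article*

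**What the plan says.** The section on the randomization procedure for 88 participants sets the block structure: "A block size of 4 will be used, dividing the sample size into 22 blocks". It describes the block contents as "predefined sequences, such as AABB, ABAB, BABA, or BBAA", and concludes that the procedure "ensures that both groups maintain equal sample sizes while preventing predictability".

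The Allocation Implementation section then describes labelling and hand-over:

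- Each treatment has one code: "Treatments A and B will be recoded by unblinded, trained faculty using either code III or code IIII".
- The code goes on the container together with the patient number: "The blind code III or IIII will be labeled on the respective patient numbers on the opaque containers".
- The containers go to the investigator: "These recoded opaque containers will then be handed over to the investigator for further administration to the patients".

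The same section relies on sequentially numbered, opaque, sealed envelopes for concealment. Staff outside enrolment and assessment prepare them. The investigator also holds 88 sealed envelopes that name each child's treatment, to stay unopened until the final visit of the trial, and codes are broken for analysis only after data lock. The Study Design section names two recruiting sites.

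**The concern.** An opaque container hides the tablets but not what is written on it. Once the group code stands beside the patient number, a sealed envelope no longer hides to which of the two groups that number belongs. With blocks fixed at four, codes already seen also determine some of those not yet seen.

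Two things are at stake. The first is selective enrolment: a person who expects a particular code next can bring a child in or hold a child back. The second is blinding: with only two codes, each constant for the whole trial, linking one code to its drug for one child links it for every child. The Sthaulya symptom grades, such as odor and perspiration, are scored by observers and are the most exposed outcomes. The Discussion relies on double blinding to control performance and ascertainment bias.

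**Working it through.** **Inputs, all from the protocol article**

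- Total 88, 44 per group; block size 4; 22 blocks (randomization procedure section).
- Sequences: AABB, ABAB, BABA and BBAA are named as examples (same section). The two other balanced sequences of four are ABBA and BAAB.
- Two codes, one per treatment, on numbered containers held by the investigator (Allocation Implementation).

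**Step 1. The plan's own figure.** 88 / 4 = 22 blocks, and 22 × 2 = 44 per group. This reproduces.

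**Step 2. Rule for certainty.** An allocation is certain if every admissible sequence that matches the codes already seen in the block gives the same next code. Certain allocations = 22 × (expected number of certain positions per block). This assumes that one person sees all earlier codes in order and knows the block size and where blocks start.

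**Step 3. All six balanced sequences.**

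- Positions 1 and 2 are never certain.
- Position 3 is certain only after AA or BB, that is in AABB and BBAA: 2 of 6 = 1/3.
- Position 4 is always certain.
- Per block: 1/3 + 1 = 1.333. Over the trial: 22 × 1.333 = 29.3 of 88 = 33.3%.
- Correct guesses when always choosing the likelier code: (1/2 + 2/3 + 2/3 + 1) / 4 = 70.8%.

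**Step 4. Only the four listed sequences.**

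- The first two codes fix the last two: AA gives BB, AB gives AB, BA gives BA, BB gives AA.
- Per block: 2 certain positions. Over the trial: 22 × 2 = 44 of 88 = 50%.
- Correct guesses: (1/2 + 1/2 + 1 + 1) / 4 = 75%.

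**Step 5. Containers held before enrolment.** If this happens, no deduction is needed, because the next code is on the label: 88 of 88.

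**Step 6. Comparators.**

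| Arrangement | Certain | Guessed correctly |
|---|---|---|
| No group code visible | 0% | 50% |
| Code visible, fixed block of 4, six sequences | 33.3% | 70.8% |
| Code visible, fixed block of 4, four listed sequences | 50% | 75% |
| Code visible, fixed block of 6, all sequences | 25% | 68.3% |
| Code visible, fixed block of 8, all sequences | 20% | 66.6% |

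A longer fixed block reduces the problem only slowly. Taking the code off the label removes it.

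**The case against.** The strongest reply is that III or IIII is not the drug. The link between code and treatment stays with faculty outside trial conduct, the treatment envelopes are sealed, and codes are broken only after data lock. That stands. A reader might infer that allocation concealment fails outright, with the investigator knowing which drug the next child will get. The documents do not support that. What they show is a partly predictable code sequence. Selection by treatment needs a second step, a guess or a disclosure, and nothing in the article shows that step occurring. The constancy of the codes does mean that the step has to happen only once.

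A reader might also infer that all 88 codes are on view in advance. The timing of hand-over is not stated, and the wording also fits containers prepared one child at a time. Nor does the article say that the investigator who holds the containers is the person who enrols; it keeps only the envelope preparers and the unblinded faculty away from those tasks.

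The counts of 29 and 44 are upper limits. If the two sites share one list, neither sees the full run of codes and fewer allocations can be deduced. The figure of 44 also treats the listed sequences as complete, although they are introduced as examples; 29 is the safer reading.

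Finally, it is tempting to argue that the tablets could be told apart by taste or smell. The article says nothing on this, so the point does not rest on it. The primary outcome, BMI, comes from measured weight and height and is less open to observer influence than the symptom grades, which are secondary.

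None of these replies rescues the statement that the procedure prevents predictability. Under the labelling described, either the next code can be read or some later codes can be deduced.

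**Conclusion.** The point holds in this limited form. Visible trial-wide codes together with fixed blocks of four make the sequence of group codes partly predictable, and the protocol's statement to the contrary is wrong.

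**Size.** Up to about 29 of 88 allocations (33%) if all six sequences are used, and up to 44 of 88 (50%) if only the four listed are used. Both assume that the enrolling person sees every earlier code in order and knows the block size. If containers are supplied before enrolment, every next code is readable. A list shared across sites would lower the deduced figures by an amount that the article does not allow one to compute.

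**Consequence.** Bias by treatment is conditional on the code being guessed or disclosed. If it is, blinding is lost for all 88 children together, including the observer-graded symptoms. This should be corrected, but it is not evidence that enrolment has been selective.

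**What to change.** 1. Label each container with the participant number, or a unique kit number, and nothing that identifies the group.
2. Keep the number-to-group key and the codes III/IIII with the unblinded faculty member until data lock.
3. Release each container only after consent and eligibility are recorded.
4. Delete or correct the statement that block randomization as described prevents predictability.

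The first two steps remove both routes, reading and deduction. Randomly varied block sizes, not disclosed to the investigator, are an optional addition for children not yet randomized.

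**Cost.** Relabelling, and a new list if block sizes are varied. The Data Monitoring Committee section has case record forms reviewed by group, so any grouping before data lock would have to come from the unblinded faculty member. With blocks of up to 6, an incomplete last block can leave the arms up to 3 children apart per list, so up to 3 + 3 = 6 overall if each site has its own list, plus up to 2 if a current block of four is abandoned part-way. The study began in April 2024 with completion planned by May 2025, so a new list can help only the children still to be randomized; new labels also help any dispensing still to come.

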### Data Collection Tools and Process

This study will use Ayurveda Samhitas (textbooks on Ayurveda), modern texts, and a web-based search of PubMed, Google Scholar, etc. Navak Guggulu (tablet) and Vachaharidradi Gana Vati (tablet) will be prepared in a GMP-certified pharmacy. The study will also use a case record form, patient information sheet, written dietary restriction, and written informed consent form. The observers will be trained properly to assess the subjective parameters and anthropometrical measurements to ensure proper data collection in the case record Form. The periodic follow-up of every fortnight for 90 days has been advocated, so the data of objective measurements and subjective criteria will be collected in case record forms every fortnight to ensure adherence. The data regarding lipid profile values will be collected before and after intervention. Quality checks will be performed manually.

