### Statistical Analysis

The statistical analysis will be performed at the end of the study. It will involve various tests to evaluate both within-group and between-group efficacy of Navak Guggulu and Vachaharidradi Gana Vati in managing Sthaulya (overweight) among children. For normally distributed continuous variables like BMI, WHR, and skinfold thickness, paired 2-tailed *t* tests will be used to evaluate the efficacy of each intervention within the same group (pre- and posttreatment comparisons).

For nonnormally distributed data, the Wilcoxon signed rank test will be used. For normally distributed data, independent 2-tailed *t* tests will be used for between-group comparisons of mean changes; for nonnormal data, the Mann-Whitney *U* test will be used.

To ensure valid comparisons, the analysis of covariance will be used to account for any potential baseline variations between groups. To evaluate residual efficacy after treatment discontinuation at 180 days, repeated measures ANOVA will analyze longitudinal changes in outcomes, while mixed-effects models will handle missing data or variability across time points. For stratified analysis based on Desha (geography), Kala (season), and Prakruti (body constitution), multivariate regression analysis will identify predictors of treatment efficacy, and interaction analysis will explore the influence of these factors. A statistician consultation will be considered for the selection of the proper statistical method.

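### The investigator's treatment-revealing envelopes may be opened after the last visit, before the data lock that governs the statistician's codes

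*Protocol article*

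**What the plan says.** All places are in the protocol article.

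- **Statistician.** Allocation Implementation: "When the data have been locked, the outcome assessor (statistician) will unblind the treatment codes for statistical analysis". The order is lock, unblinding, analysis.
- **Investigator.** The same section gives the investigator 88 sealed envelopes, each disclosing one child's treatment. They are to be "kept intact under the investigator’s custody until the completion of the last visit of the last enrolled patient". Data lock is not mentioned for them.
- **Codes.** "Treatments A and B will be recoded by unblinded, trained faculty using either code III or code IIII". The code is written on the containers against the patient numbers, and the containers go to the investigator.
- **Data handling.** Data Collection Tools and Process: "Quality checks will be performed manually". No time is given. Data Monitoring Committee includes the researcher and has supervisors and statisticians review forms and master charts by group. Ethical Considerations restricts data access to the research team.
- **Analysis.** Statistical Analysis names the independent t test or the Mann-Whitney U test according to normality, and adds that "the analysis of covariance will be used to account for any potential baseline variations between groups". It also says: "A statistician consultation will be considered for the selection of the proper statistical method".

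**The concern.** A double-blind trial normally keeps everyone who can change the data blind until the data are fixed. Here the person furthest from the data, the statistician, is held blind until lock. The person closest to them, the investigator, is held blind only to the last visit. If checks or corrections take place between those two times, they may be made by people who know the arms.

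The entries most open to this are those that rest on judgement. Table 4 grades symptoms such as body odour, sweating and exertional breathlessness by impression. Ethical Considerations removes children whose condition worsens, or whose other illness or personal circumstances are thought likely to affect the results. Measured BMI is harder to move, but who is counted in the BMI comparison depends on those exclusions. A reader of the final report could not rule out that late corrections were made with the arms known.

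**Working it through.** **1. The two release points side by side.** The plan gives no figure for this point, so the check is one of order in time.

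| Event | Investigator's 88 envelopes | Statistician's codes |
|---|---|---|
| Up to the last child's last visit | sealed | closed |
| Last visit to data lock | **opening not barred** | closed |
| After data lock | opening not barred | opened for the analysis |

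Let T1 be the last visit (day 180 of the last child) and T2 the lock. The gap is T2 − T1 ≥ 0. The article gives neither date. If lock were declared on the day of the last visit, the gap would be nil; any later cleaning makes it positive.

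**2. How much one opened envelope reveals.** There are only two codes, each standing for a whole arm, and the code is on every child's container. One envelope links one child's code to a treatment. That identifies the other code too, and so the arm of all 88 children whose container codes are known.

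**3. What could still change in the gap.** Manual quality checks are undated, so they may fall on either side of T1. Most exclusions should be settled earlier: treatment ends at day 90, which is 180 − 90 = 90 days before the last child's last visit. What remains is late reclassification of exclusions, and queries on symptom grades, including those from day 180.

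**4. What analysis under codes III and IIII would add.** Equivalence is declared when the confidence interval (L, U) for the difference lies inside (−m, m). Swapping the arms turns (L, U) into (−U, −L), which lies inside (−m, m) exactly when (L, U) does. The decision therefore does not depend on which arm is which.

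This was checked by simulation: 44 per arm, SD of change 0.86, m = 0.57, true difference at the margin, 95% interval, and 4,000 trials at each of three baseline–change correlations. The 0.86, 0.57 and 44 are the protocol's. Reading 0.57 as the margin, and the correlations, are assumptions.

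| Correlation | t test | Mann-Whitney interval | ANCOVA | Best of the three |
|---|---|---|---|---|
| 0 | 2.53% | 2.40% | 2.48% | 3.15% |
| −0.3 | 2.60% | 2.45% | 2.30% | 3.45% |
| −0.5 | 2.25% | 2.45% | 2.33% | 3.90% |

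Entries are rates of falsely declaring equivalence. Swapping the labels changed the decision in 0 of 3 × 4,000 = 12,000 trials. Picking the most favourable test raises the rate, but an analyst could do that equally well with coded arms.

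Identity does matter elsewhere. Primary Objectives 1 and 2 are separate efficacy claims for each drug, tested within arm, and a 2-tailed between-arm test invites a statement about which drug did better. Those are the readings that coding protects.

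**5. Sample size.** Release times do not enter the sample-size formula, so sample size, alpha and power stay as they are.

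**The case against.** Three objections carry weight.

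- **There is no contradiction.** The envelope sentence sets a minimum period of sealing and does not order the envelopes opened when it ends. Both sentences can be obeyed together. This stands: the defect is a gap in protection, not two statements that conflict.
- **Post-lock unblinding is normal.** It is, and the protocol never promises a coded analysis. This stands as well; coding is an optional extra.
- **The timing of the quality checks is conjecture.** The sentence on manual checks has no date, and the master chart is said to be kept securely with limited access. It stands that nothing shows corrections after the last visit. But nothing excludes them either, and the protocol itself sets both release times, so this is not a detail left to an analysis plan that is not shown.

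A reader might also infer more than the documents support:

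- *That the test is chosen after the arms are known.* The statistician consultation has no date, and an analysis plan may fix the method earlier.
- *That coded labels would prevent selection among tests.* For the equivalence question they would not, as the label swap shows.
- *That four or more methods compete for the BMI comparison.* Repeated measures ANOVA and the mixed model are introduced for residual efficacy at 180 days. The t test, Mann-Whitney U and ANCOVA remain, and the first two form one rule decided by normality.
- *That the stated hope of patenting and commercialising the trial drug shows bias.* It shows an interest, not a defect in design.

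**Conclusion.** The concern holds in a limited form. As worded, the protocol permits the study team to be unblinded between the last visit and data lock, while the statistician is not. That leaves data checks and judgement-based corrections in the interval unprotected.

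The size cannot be computed: it depends on the length of the gap, on whether envelopes are in fact opened in it, and on how many entries are changed. It ranges from nothing, if lock coincides with the last visit or the envelopes stay closed, to a real risk for symptom grades and for the set of children analysed. The conclusion assumes only that lock may follow the last visit by some interval and that checks may continue in it.

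Opening the statistician's codes after lock is not an error. Coded analysis is worth having for within-arm and directional readings, but it is a minor addition.

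**What to change.** In Allocation Implementation, replace the last-visit condition on the envelopes with one release point for envelopes and codes alike. Possible text:

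> Routine unblinding, by envelope or by treatment code, takes place at one time only. That time is never before data lock and is preferably after the between-arm and within-arm analyses have been run and signed off under codes III and IIII.

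This concerns routine release only. The faculty member who assigns the codes can hold the key until then.

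The cost is wording: the codes and envelopes already exist, the analysis work is the same, and sample size, alpha and power do not change. The change does not deal with choice among tests; that is answered by naming one primary between-arm analysis before the codes open, which an analysis plan not shown here may already do.

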### Data Collection Tools and Process

This study will use Ayurveda Samhitas (textbooks on Ayurveda), modern texts, and a web-based search of PubMed, Google Scholar, etc. Navak Guggulu (tablet) and Vachaharidradi Gana Vati (tablet) will be prepared in a GMP-certified pharmacy. The study will also use a case record form, patient information sheet, written dietary restriction, and written informed consent form. The observers will be trained properly to assess the subjective parameters and anthropometrical measurements to ensure proper data collection in the case record Form. The periodic follow-up of every fortnight for 90 days has been advocated, so the data of objective measurements and subjective criteria will be collected in case record forms every fortnight to ensure adherence. The data regarding lipid profile values will be collected before and after intervention. Quality checks will be performed manually.

### Outcomes

#### Primary Outcome—BMI

BMI will be calculated as the ratio of body weight to the square of height (kg/m^2^). Indian Academy of Pediatrics 2015 charts will be used to categorize weight as normal, overweight, and obese.

#### Secondary Outcome

The secondary outcomes are as follows: (1) anthropometric measurements including mid-upper arm circumference, abdominal girth, waist circumference, hip circumference, and WHR in children with overweight; (2) reduction in lipid profile values in children with overweight; and (3) reduction of signs and symptoms of obesity (Sthaulya) mentioned in Ayurvedic classics following the gradations in the book called WHO-Direct Financial Cooperation sponsored project on Developing Guidelines for Clinical Research Methodology in Ayurveda [43].

